## **7.3 Accrual and duration of study**

Estimated accrual for this study is 3 patients a month. Thus, patient accrual is expected to be completed within 12 – 14 months. Additional time is required to allow the response data to mature. Expected duration of follow-up after the end of accrual is 12 months (no maximum).

## **7.4 Missing data**

All of the patients registered in the study will be accounted for. The number of patients who were not evaluable, who died or withdrew during follow up will be specified and censored. The distribution of follow up time will be described and the number of patients lost to follow-up will be given.

## 8 Translational research

### 8.1 Objectives of the translational research study

#### 8.1.1 Pharmacokinetics/imaging kinetics of Zr-cetuximab

Five patients will have in total 5 immuno-PET scans at 1h, day 2, 3, 4 and 7 after administration of Zr-cetuximab with concomitant blood samples at each scan time point to do the pharmacokinetics and imaging kinetics of Zr-cetuximab.

#### 8.1.2 To explore the potential association between EGFR saturation with cetuximab and treatment outcome

EGFR is highly expressed in epidermal tissue, and thus is expected to bind a large amount of cetuximab. We are interested to explore the level of saturation with the hypothesis that a high level of saturation may well be associated with a high uptake in tumor lesions and with response to treatment. If future trials would confirm such a relationship, saturation of epidermal EGFR with cetuximab may be used as predictive marker for treatment response to cetuximab.

An immunohistochemistry assay using cetuximab on snap-frozen tissue biopsies has been developed by Shin et al to investigate this (Shin 2001). We have experience with this assay at our laboratory. We will perform this assay on the snap-frozen skin biopsies.

#### 8.1.3 To investigate kinase activity in skin samples before and after treatment with cetuximab

Microarrays of kinase substrate peptides have been developed to study cellular signal transduction by detecting up and downregulation of kinase activity in an array based format (such as PamChip® array, validated by Sikkema et al 2009). By generating information on kinase-induced peptide phosphorylation, these arrays may provide new insights into specific downstream signaling pathways. Ideally, kinase peptide substrate arrays provide kinase activity values across the kinome.

Kinase peptide substrate arrays consist of immobilized peptides containing Ser, Thr or Tyr residues with additional sequence context for phosphorylation by their upstream kinases and can therefore reveal kinase activity *in-vitro*. After incubating the array with cell lysate, phosphorylation is determined by fluorescence microscopy (anti-phospho antibodies). Spot intensities can subsequently be correlated with kinase activity ([name], [name] et al pers comm).

By analyzing skin biopsies, which express significant amounts of the EGFR receptor, we hope to identify changes in kinase activity before and after treatment with cetuximab, which potentially improves our understanding of the mechanism of action of this antibody and as such can assist in improving anti EGFR-therapy.

### 8.2 List of the material to be obtained for each patient

#### 8.2.1 Blood samples

From 5 patients blood samples (20 ml) will be collected at 0-2h, on day 2, 3, 4 and 7, from the remaining patients a blood sample will be collected at 0-2h and on day 4 or 7 for pharmacokinetic purposes.

### **8.2.2 Skin biopsies**

Optional (separate consent form)

If a patient has agreed to have a skin biopsy, a punch biopsy of the skin will be performed within 14 days before start of cetuximab treatment and after 3-4 weeks of treatment.

## **8.3 Instructions for treating and storing samples**

### **8.3.1 Blood samples**

The blood samples will be collected and stored according to local practice in our research facility.

### **8.3.2 Skin tissue specimen**

Immediately after skin biopsy, tissue will be snap frozen in liquid nitrogen and stored at -80 °C in our research facility. Next, cryoslides of frozen tissue will be made for the lysis procedure as well as for H&E staining and immunohistochemistry analysis.

The lysis procedure includes addition of a sample buffer with protease inhibitors and phosphatase inhibitors to a cryoslides containing vial. After centrifugation the supernatant will be aliquotted and stored at -80. A small sample (1 or 2 µl) will be used for protein quantification. The lysate will be used for the PamChip®.

The immunohistochemistry analysis will be performed as described by Shin et al (Shin 2001).

## **9 Safety reporting**

### **9.1 Section 10 WMO event**

In accordance to section 10, subsection 1, of the WMO, the investigator will inform the subjects and the reviewing accredited METC if anything occurs, on the basis of which it appears that the disadvantages of participation may be significantly greater than was foreseen in the research proposal. The study will be suspended pending further review by the accredited METC, except insofar as suspension would jeopardize the subjects' health. The investigator will take care that all subjects are kept informed.

### **9.2 Adverse and serious adverse events**

Adverse events are defined as any undesirable experience occurring to a subject during a clinical trial, whether or not considered related to the investigational drug. All adverse events reported spontaneously by the patient or observed by the investigator or his staff will be recorded.

A serious adverse event is any untoward medical occurrence or effect that at any dose results in death;

- is life threatening (at the time of the event);
- requires hospitalization or prolongation of existing inpatients' hospitalization;
- results in persistent or significant disability or incapacity;
- is a congenital anomaly or birth defect;

All SAEs will be reported to the accredited METC that approved the protocol, according to the requirements of that METC.

### **9.3 Annual safety report**

The investigators will submit, once a year throughout the clinical trial, a safety report to the accredited METC.

### **9.4 Follow-up of adverse events**

All adverse events will be followed until they have abated, or until a stable situation has been reached. Depending on the event, follow up may require additional tests or medical procedures as indicated, and/or referral to the general physician or a medical specialist.

## **10 Ethical considerations**

### **10.1 Patient protection**

The study will be conducted according to the principles of the declaration of Helsinki and in accordance with the Medical Research Involving Human Subjects Act (WMO).

Subjects will be identified in the trial database by unique anonymous identification numbers.

### **10.2 Informed consent**

The informed consent document will be used to explain the risks and benefits of study participation to the patient in simple terms before the patient is entered into the study. It will be emphasized that participation is voluntarily and consent can be retracted at any time.

The investigator is responsible to see that informed consent is obtained from each patient and to obtain the appropriate signatures and dates on the informed consent document prior to the performance of any protocol procedures and prior to the administration of study drug.

### **10.3 Benefits and risks assessment**

#### **10.3.1 Risks**

Use of positron emitting radionuclides means exposure to ionizing radiation. The total effective dose of one administration of Zirconium-89 MAb will be about 20 mSv. Low-dose CT will deliver 3 mSv per CT. [18F]-FDG yields a radiation dose of 3.3 mSv for 185MBq.

When considering the justification of application, a risk to benefit analysis has to be performed. ICRP-62 provides a model for this. According to this model, the risk level corresponds to “moderate”, while the social benefit corresponds to “substantial”.

After injection of the conjugate no shielding is required, and the patient can go directly home without further limitations. The risks of cetuximab are well-known as this drug is used in routine clinical practice (see above for detailed description). The first 6 months after the study both males and females are advised to prevent pregnancy.

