## **2.2 Immuno-PET**

The introduction of immuno-positron emission tomography (PET), the combination of PET with mAbs, is an attractive novel option to visualize molecular interactions. In advanced CRC patients, treatment with cetuximab labeled with a positron emitter has the potential for quantification of the interactions of the drug within the different compartments of the body, including metastases. The positron emitters Zr ( $t_{1/2} = 78.4$  h) is particularly well suited for imaging of slow kinetic intact antibodies because its long half-lives allows imaging at late time points for obtaining maximum information. VUmc has obtained a leading position in immuno-PET imaging by the introduction GMP (good manufacturing practice)-compliant procedures for the production and purification of positron emitters like Zr, by the development of universal procedures for stable coupling of this positron emitters to MAb, and by performing preclinical and clinical safety and proof of principle studies. There is no shielding required and the patient can go home directly. The first two days, the patient is not allowed in the proximity of children and pregnant women. Additional information regarding Zr cetuximab can be found in SECTION 6.

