#### Radiation exposure

For the patient the total dose of Zirconium-89 is 37 MBq. After injection no shielding is required, and the patient can go directly home. There are no limitations to the adult residence of the patients. However the first 2 days the patient is not allowed in the proximity of children and pregnant women, and the first two weeks restricted to spend more than 4 hours a day in the same room with children and pregnant women. Also the first week it is advised to retain distance to children and pregnant women.

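### Protocol section 10.3.1 says no limitations apply after the 89Zr-cetuximab injection, which contradicts the contact restrictions in sections 6.1 and 2.2

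*Protocol*

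**What the plan says.** Three places in the protocol describe what applies to the patient after the tracer has been injected.

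- **Section 10.3.1, Risks:** after stating that no shielding is needed, it says that "the patient can go directly home without further limitations".
- **Section 6.1, Radiation exposure:** this text also says that no shielding is needed and that the patient may go home. It then states "There are no limitations to the adult residence of the patients", and its next sentence begins "However the first 2 days the patient is not allowed in the proximity of children and pregnant women". That sentence continues with "the first two weeks restricted to spend more than 4 hours a day in the same room with children and pregnant women", and the paragraph ends with "Also the first week it is advised to retain distance to children and pregnant women".
- **Section 2.2, Immuno-PET:** "The first two days, the patient is not allowed in the proximity of children and pregnant women". The paragraph closes by sending the reader to Section 6 for more about the tracer.

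**The concern.** The same injection is followed by no limitation in one section and by restrictions on contact in two others. The restrictions protect children and pregnant women around the patient, who are not trial participants. Anyone who took 10.3.1 as it stands would drop a precaution that 6.1 and 2.2 require. Section 10.3.1 is also the text in which the protocol sets out the radiation risk of taking part, so readers who want to know what participation entails are likely to turn to it. That makes the discrepancy more than a clerical slip, although it has no statistical consequence.

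**Working it through.** No arithmetic applies. The check is a comparison of the three texts, item by item.

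1. **Shielding.** Sections 10.3.1, 6.1 and 2.2 all say that none is required. They agree.
2. **Going home.** All three say that the patient can leave directly. They agree.
3. **First two days, proximity to children and pregnant women.** 6.1: not allowed. 2.2: not allowed. 10.3.1: no limitation. **They conflict.**
4. **First week, distance from children and pregnant women.** 6.1: advised. 2.2: silent, with a reference to Section 6. 10.3.1: no limitation. **10.3.1 conflicts with 6.1.**
5. **First two weeks, same room for more than 4 hours a day.** 6.1: restricted (the sentence is awkward, but a ceiling of 4 hours is its natural meaning). 2.2: silent, with the same reference. 10.3.1: no limitation. **10.3.1 conflicts with 6.1.**
6. **Adult contacts.** 6.1: no limitation. 2.2: nothing stated. 10.3.1: no limitation of any kind. There is no conflict here.

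Sections 6.1 and 2.2 therefore never disagree: on the one item that both cover (item 3), they give the same rule. Section 10.3.1 disagrees with at least one of them on items 3, 4 and 5.

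Next, does anything else in the protocol qualify 10.3.1?

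- The sentence itself carries no exception and no cross-reference. The only pointer to other text in that paragraph concerns the known risks of cetuximab.
- The paragraph's one further precaution is advice to prevent pregnancy for 6 months after the study. That is not about contact with other people.
- The burden paragraph of the Summary (section 1) says only that shielding is not required. It is silent on contact, so it neither repeats nor corrects the statement in 10.3.1.
- The text on the labelled infusion in section 5.4.1 refers users to Section 6 for details of the tracer, but does not mention 10.3.1.

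The conflict is therefore not resolved anywhere in the document.

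On reach, section 7.2.2 plans 35 patients plus 3 for drop-outs, 35 + 3 = 38, including those of part one. The discrepancy applies to each patient who is injected.

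**The case against.** The best defence is that 10.3.1 is a shortened copy of the opening of the 6.1 paragraph, meant to cover only shielding, discharge and adult contacts. That may well be how it arose. It does not rescue the sentence. Shielding and discharge are already dealt with in its earlier words, so the closing phrase adds a separate claim. The adult qualifier is also absent, as is the contrasting sentence that follows it in 6.1.

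A second objection is that staff would work from the dedicated radiation text in 6.1 and not from the ethics chapter, particularly since 2.2 and 5.4.1 both point to Section 6. This has force. The protocol does contain the fuller precaution in the place where one would look for it, and nothing shows that the wording in 10.3.1 ever reached practice. It limits the likely consequence without removing the contradiction.

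Three stronger readings may suggest themselves, and the document does not support them.

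- **That the protocol gives three different instructions.** It does not. Section 2.2 gives the first of the rules in 6.1 and refers to Section 6 for more. A short mention of that kind is incomplete, not contradictory.
- **That the risk classification in 10.3.1 is undermined.** That weighing follows effective doses and an ICRP-62 category. Nothing indicates that household contact rules enter it or would change it. The dose of about 20 mSv given there is the patient's own and does not measure exposure of others.
- **That patients were wrongly informed.** The consent pages are not available for this review, so nothing can be said about them either way.

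**Conclusion.** The contradiction is real and lies in one place: the statement in 10.3.1 that no limitations follow the injection is incompatible with 6.1 and with 2.2. It covers all three of the precautions in 6.1, one of which 2.2 repeats, and it applies to every injected patient. The conclusion rests on the plain wording of current text and on no numerical assumption. It should be corrected because the precaution concerns the safety of third parties. Endpoints, sample size and analysis are unaffected. This review takes no view on which statement is right.

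**What to change.** Reconcile 10.3.1 with 6.1 and 2.2. One workable form is a single governing statement on contact after injection, with the other sections referring to it; identical wording in all three places is not needed. The responsible radiation-safety function should decide what that statement says. The patient information should then be checked against it. The cost is a sentence or a cross-reference in the protocol and one document check, with no effect on data collection, sample size or timelines for analysis.

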#### **10.3.2 Potential benefits**

Cetuximab has been approved as 3rd line treatment for advanced CRC with K-Ras wild type status. Results from recent phase II and III trials have shown that cetuximab is an effective treatment for these patients.

## 11 Trial insurance

The sponsor/investigator has a liability insurance which is in accordance with article 7, subsection 6 of the WMO.

The sponsor (also) has an insurance which is in accordance with the legal requirements in the Netherlands (Article 7 WMO and the Measure regarding Compulsory Insurance for Clinical Research in Humans of 23th June 2003). This insurance provides cover for damage to research subjects through injury or death caused by the study.

1. € 450.000,-- (i.e. four hundred and fifty thousand Euro) for death or injury for each subject who participates in the Research;
2. € 3.500.000,-- (i.e. three million five hundred thousand Euro) for death or injury for all subjects who participate in the Research;
3. € 5.000.000,-- (i.e. five million Euro) for the total damage incurred by the organization for all damage disclosed by scientific research for the Sponsor as 'verrichter' in the meaning of said Act in each year of insurance coverage.

The insurance applies to the damage that becomes apparent during the study or within 4 years after the end of the study.

### Data management

CRFs for the recording of all data will be developed by the data manager of the VUMC. The forms will be printed on normal paper and the original CRFs will be retained by the investigator. Data should be recorded legibly onto the CRF in black, permanent ink, ballpoint pen. Corrections should be made legibly and initially and dated by approved personnel, the reasons for significant changes must be provided. Correction fluid or covering labels must not be used.

CT and MRI data will be stored at the IMS-server for at least two years after the last patient of the study has been evaluated or longer if necessary.

Immuno-PET-CT data will be stored in regular diagnostic databases of the nuclear medicine department.

## **Amendments**

Amendments are changes made to the research after a favorable opinion by the accredited METC has been given. All amendments will be notified to the METC that gave a favorable opinion.

A 'substantial amendment' is defined as an amendment to the terms of the METC application, or to the protocol or any other supporting documentation, that is likely to affect to a significant degree:

- the safety or physical or mental integrity of the subjects of the trial;
- the scientific value of the trial;
- the conduct or management of the trial; or
- the quality or safety of any intervention used in the trial.

All substantial amendments will be notified to the METC and to the competent authority.

Non-substantial amendments will not be notified to the accredited METC and the competent authority, but will be recorded and filed by the sponsor.

## **Annual progress report**

The investigator will submit a summary of the progress of the trial to the accredited METC once a year. Information will be provided on the date of inclusion of the first subject, numbers of subjects included and numbers of subjects that have completed the trial, serious adverse events/ serious adverse reactions, other problems, and amendments.

## **End of study report**

The investigator will notify the accredited METC of the end of the study within a period of 8 weeks. The end of the study is defined as the last patient's last visit.

In case the study is ended prematurely, the investigator will notify the accredited METC, including the reasons for the premature termination.

Within one year after the end of the study, the investigator/sponsor will submit a final study report with the results of the study, including any publications/abstracts of the study, to the accredited METC.

# **13 Trial sponsorship and financing**

Investigator-initiated study.

Financing: Department of Medical Oncology, Department of Nuclear Medicine and PET research, Department of Otolaryngology/Head and Neck Surgery; VU University Medical Centre.

# **14 Publication policy**

With the exception of personal and confidential medical records, all data generated under the trial shall be the property of the investigator. The investigator will publish or present the data generated in the study in accordance with accepted scientific practice.

The trial-coordinator and the principal investigator together with the co-investigators will prepare the manuscript reporting the final results.

